**Inclusion criteria:**

- Participants with controlled type 2 diabetes mellitus who are on medication.
- Participants with diabetes mellitus whose blood glucose level is above 250 mg/dl will be screened for ketone bodies.
- Aged between 30-65 years of both male & female

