Evaluation of insulin resistance and β-cell function is important for understanding the disease status. The gold standard of evaluation of insulin sensitivity is glucose clamp test.(Okita et al., 2013) The various methods to measure insulin resistance are Hyperinsulinemic euglycemic glucose clamp, oral glucose tolerance test (OGTT) Fasting insulin, Glucose/Insulin ratio, Insulinogenic index (IGI), Homeostatic model assessment , Quantitative insulin sensitivity check index (QUICKI), Minimal model analysis of frequently sampled intravenous glucose tolerance test, Glucose insulin (GI) product, Fasting insulin Resistance Index (FIRI).Most of these methods employed are difficult to apply in clinical practice.(Singh & Saxena, 2010)

Most commonly used measures are Fasting Insulin and Homeostatic Model Assessment –Insulin Resistance (HOMA-IR). Fasting Insulin which is been considered as the most practical approach for the measurement of Insulin Resistance. Homeostatic Model Assessment –Insulin Resistance (HOMA-IR) which is calculated from fasting plasma glucose level and immunoreactive insulin (IRI) is a simple method for evaluation of Insulin resistance.(Singh & Saxena, 2010)

A possible hypothesis is that hyperglycemia, which is an early manifestation in the development of diabetes damages muscle which results in loss if strength and mass. Loss of muscle strength is also an important predictor of physical function and disability in diabetes mellitus. It is associated with excess physical disability in older adults especially in the lower extremity mobility tasks. But the relationship between the diabetes mellitus and loss of muscle strength has not been fully studied.(Kalyani, Metter, Egan, Golden, & Ferrucci, 2015)

Previous studies has reported a decline in thigh muscle cross sectional area (CSA) of 25-40% over the life span of the patient and also seems to be in line with other studies reporting a 30% reduction in leg muscle mass.(Nilwik et al., 2013)

Previous observational studies have described the cross sectional association of fasting and 2 hour post -75 oral glucose tolerance test levels (insulin levels) with loss of muscle mass and strength in person with and without diabetes.(Kalyani et al., 2015)

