**Investigator:**

Physiotherapist pursuing his structured Ph.D. program.

- **Sample size:** Sample size calculated based on the ***Fasting insulin level*** outcome measure

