**Exclusion criteria:**

- - Participants with type 1 diabetes mellitus
  - Any significant respiratory disease, coronary artery disease, neurological disorders, musculoskeletal problems that would interfere with the exercise training,
  - Pregnancy
  - Thyroid disorder
  - Participants not willing to participate in exercise protocol

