**Source: *Acsm Guidelines for Exercise Testing and Prescription 9^th^ edition***

**Consort of Phase – I**

- Permission will be sought from Institutional Research Committee and Institutional Ethical Committee and trial will be registered under CTRI. All participants will be screened for insulin resistance Informed consent will be obtained from the participants who are willing to take part in the study
- Participants will be clinically and biochemically evaluated for following outcomes

**Primary outcome**: Fasting Insulin Level, HOMA-IR, WHOQOL- BREF, Six minute walk test

**Secondary outcome:** Body composition analysis, Fasting blood sugar, GPAQ, HbA1c.

The participants will be randomized into study group and control group (Block Randomization)

Control Group

Study group

No structured exercise program will be given to the control group participants

Study group participants will be given a set of exercise programs along with the standard care.

Standard hospital care will be advised to the participants

Adherence to exercise will assessed by telephonic call, log book and check list will be given to all the participants

Participants will be asked to continue routine work

After 6 weeks progression of exercise program will be prescribed by the principal investigator

Reassessment of all outcome measures will be done at 3 month

Reassessment of all outcome measures will be done at 3 month

Data will be analyzed

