**Primary outcome measures:**

- Fasting insulin level [ mIU/L]
- HOMA-IR
- Six minute walk test
- Quality of life by WHOQOL-BREF

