**Data analyses:**

- Data will be analysed using SPSS version 15
- Paired t test will be used to analyse within the groups & independent t test is used between the groups
- Descriptive statistics will be used to analyse the age, GPAQ & body composition
- Level of significance will be set at p<0.05

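### Eligibility admits patients treated with insulin, so fasting insulin (the powering outcome) and HOMA-IR can partly reflect injected insulin in any such patients enrolled

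*Protocol*

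**What the plan says.** **Who may enter.** The protocol's Inclusion criteria admit "Participants with controlled type 2 diabetes mellitus who are on medication", aged 30 to 65. No drug class is named. The Exclusion criteria start with "Participants with type 1 diabetes mellitus" and go on to interfering comorbidity, pregnancy, thyroid disorder and unwillingness to exercise. Insulin therapy is not mentioned in either list.

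**How they are allocated.** Under Consort of Phase – I: "The participants will be randomized into study group and control group (Block Randomization". Neither that section nor the Randomization line under Sample size gives a stratification factor.

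**What is measured.** The primary outcomes are "Fasting Insulin Level, HOMA-IR, WHOQOL- BREF, Six minute walk test". The first objective uses fasting insulin as its measure of insulin resistance, and the Sample size entry reads "Sample size calculated based on the *Fasting insulin level* outcome measure". The Introduction describes HOMA-IR as an index "which is calculated from fasting plasma glucose level and immunoreactive insulin (IRI"), so both insulin-resistance outcomes depend on the same measured insulin.

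**How it is compared.** Data analyses states: "Paired t test will be used to analyse within the groups & independent t test is used between the groups".

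The protocol does not give the time of blood sampling relative to the last injection, the insulin assay or a C-peptide measurement. It does not ask for glucose-lowering treatment to be recorded during follow-up.

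**The concern.** Fasting insulin serves as a marker of insulin resistance when the insulin measured is the patient's own. In a patient who injects insulin, the measured value can also depend on the product, the amount and the time since the last dose. A change over 3 months may then reflect a change of treatment rather than of insulin sensitivity. HOMA-IR takes the same value as an input and has the same weakness.

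At stake is the insulin-resistance half of the trial's aim, including the outcome that sets the sample size. The expected harm is extra variability and a weaker link between the outcome and the question, with a true exercise effect diluted as a result. The Consort of Phase – I section also says that participants are screened for insulin resistance, without naming the method. If the screen uses fasting insulin or HOMA-IR, it shares the problem.

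**Working it through.** **1. Inputs from the protocol (Sample size).** z for significance 1.96, z for power 0.84, SD 8.26, difference 2, stated size 120 per group with 20% dropout. The share of insulin users, their mean fasting insulin, their variability and the source of the SD are not given.

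**2. The plan's own figure.** N = 2(1.96 + 0.84)² × 8.26² / 2² = 15.68 × 68.23 / 4 = 267.45, so 268 evaluable per group, and 268 / 0.8 = 335 with dropout. The stated 120 is not reproduced. That is a separate defect. Below, 267.45 is the reference, so that the two problems are not mixed.

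**3. Dilution (assumed).** Let p be the share of insulin users. Suppose the effect is 2 mIU/L in non-users, fasting insulin in users carries no exercise signal, and the SD stays at 8.26. The average effect is 2(1 − p), and the required N grows by 1/(1 − p)².

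| p | Average effect (mIU/L) | Inflation of N | Evaluable N per group |
| --- | --- | --- | --- |
| 0 | 2.0 | 1.00 | 268 |
| 0.1 | 1.8 | 1.23 | 267.45 / 0.81 = 330.2, so 331 |
| 0.3 | 1.4 | 2.04 | 267.45 / 0.49 = 545.8, so 546 (547 with unrounded normal quantiles) |

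**4. Added variance (assumed, separate from step 3).** Suppose 8.26 describes non-users, users' mean is higher by s, and injected insulin adds an SD of x among users. Then pooled SD = √(8.26² + p·x² + p(1 − p)·s²).
- p = 0.1, s = x = 5: √(68.23 + 2.5 + 2.25) = 8.54, and N for a difference of 2 is 287 per group.
- p = 0.3, s = x = 20: √(68.23 + 120 + 84) = 16.5, and N is about 1,070 per group.

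The width of this range shows how little the documents fix. If 8.26 came from a sample that already included insulin users, part of this variance is already counted.

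**5. Chance imbalance.** Under simple randomisation with 120 per group, the difference in the share of users between arms has SD √(2p(1 − p)/120): 0.039 at p = 0.1 and 0.059 at p = 0.3. That is about 4 to 6 percentage points. Stratification would largely remove it.

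**6. Does restricting to non-users help?** If the insulin-based comparison uses only baseline non-users, the effect stays at 2 and the number randomised must be 267.45/(1 − p): 298 per group at p = 0.1 and 383 at p = 0.3. Under step 3 the pooled analysis needs 331 and 546. Restriction is more efficient even though it uses fewer participants.

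**The case against.** **Enrolment of insulin users is inferred.** A reader might take the criteria to mean that insulin users will be recruited. The text only permits it. This stands, and the point is conditional on it.

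**The size rests on assumptions.** The 10-30% share and the absent signal in users are not in the documents. The protocol presents 2 as the clinically significant difference for the whole comparison, not for non-users. This also stands: the figures are illustrations.

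**Low power should not be charged to this point.** With 120 × 0.8 = 96 evaluable per group, power for a difference of 2 is about 39%, and the dilution above lowers it to 33-22%. A reader might blame insulin use for those figures. Most of the shortfall comes from the separate sample-size error; dilution accounts for about 6 to 17 percentage points. Restriction would leave about 86 to 67 of the 96 and give about 36-29%. That gain is modest, but it is a gain.

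**Bias by arm is not shown.** A reader might infer that, because participants know whether they exercise, insulin treatment will drift apart between arms and pass as an exercise effect. The protocol says nothing on blinding of prescribers, describes standard care in both groups, and gives no evidence of differential change. Randomisation balances baseline insulin use on average. Changes in other glucose-lowering drugs could also differ by arm, and excluding insulin users would not prevent that.

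**The outcome may still be usable in insulin users.** The effect of injected insulin on the result depends on unstated assay and timing details. The reference list contains a paper on HOMA-IR in patients with type 2 diabetes on insulin therapy. Its title alone settles nothing, but a flat claim that the measure is invalid would go too far.

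**Some of the remedy belongs in a statistical analysis plan.** Adjustment and analysis sets are commonly set there, and none is at hand, so their absence is not held against the protocol. Eligibility, stratification and the data to be collected are protocol matters.

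**Conclusion.** The point holds as a limited one about validity and noise. As written, the criteria let insulin-treated patients into a trial whose insulin-resistance question is answered by fasting insulin and HOMA-IR. In any such patients, both can partly reflect injected insulin, to an extent that the documents do not allow one to judge.

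It would be wrong to read this as a failure of the primary outcomes as a whole: quality of life and walking distance, the other two of the four, are not touched. Nor do the documents show a systematic bias, which would require insulin treatment to change differently by arm.

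The size is illustrative. With 10-30% insulin users and no exercise signal in their fasting insulin, the average effect falls to 1.8-1.4 mIU/L and the required number rises about 1.2- to 2.0-fold. Added variance could increase that further if the SD of 8.26 describes non-users. All of this is separate from the mismatch between the sample-size formula and the stated 120 per group.

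**What to change.** Add current insulin therapy to the Exclusion criteria. This is one line. It costs a somewhat smaller recruitment pool and narrower generalisability.

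If insulin users are wanted for the quality-of-life and walk-test outcomes, keep them and make three changes:
- Stratify the block randomisation by insulin use at baseline.
- State that the primary fasting insulin and HOMA-IR comparisons are made in participants not on insulin at baseline. Because the subset is defined before randomisation, the comparison remains a randomised one.
- Record glucose-lowering medication at baseline and 3 months and tabulate changes by arm. The baseline restriction does not remove participants who start insulin during follow-up, and this record makes them visible.

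The cost of this option is one stratification factor, a short medication form at two visits, and fewer participants in the insulin-based analyses. The corrected sample size should allow for that loss by dividing the evaluable number by the expected share of non-users.

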**Exclusion criteria:**

- - Participants with type 1 diabetes mellitus
  - Any significant respiratory disease, coronary artery disease, neurological disorders, musculoskeletal problems that would interfere with the exercise training,
  - Pregnancy
  - Thyroid disorder
  - Participants not willing to participate in exercise protocol

**Materials:**

- Bioelectrical Impedence Analysis
- Radio-telemetric heart rate monitor
- Inch tape (non-stretchable)
- Skin fold caliper
- Treadmill
- Weighing scale
- Measuring tape

**Protocol:**

**General guidelines for exercise in Type 2 Diabetes Mellitus:**

Before undergoing any exercise regime a pre-exercise evaluation is required to rule out diabetes related health complications. For individuals desiring to participate in low-intensity physical activity (PA) such as brisk walking, conducting exercise stress testing before walking is unnecessary and moreover no evidence suggests that it is routinely necessary as a CVD diagnostic tool, and requiring it may create barriers to participation among patient population**.**

**AEROBIC & RESISTANCE EXERCISE TRAINING**

| **VARIABLE** | **T2DM** |
| --- | --- |
| Frequency | 3 days / week aerobic exercise  2 days / week of resistance exercise |
| Intensity | 40-85% HRR [Aerobic Exercise] , 60-80% 1 RM [Resistance Exercise]  RPE = 11-16 |
| Time | Aerobic: 30-60 mins per session  Resistance :8-12 reps/ exercise, 1-3 sets/exercise |
| Type of exercise | Aerobic : Brisk Walking , running , cycling  Resistance : All major muscle groups  Upper body: 4-5 exercises  Lower body/core: 4-5 exercises |

**Source: *Acsm Guidelines for Exercise Testing and Prescription 9^th^ edition***

**Consort of Phase – I**

- Permission will be sought from Institutional Research Committee and Institutional Ethical Committee and trial will be registered under CTRI. All participants will be screened for insulin resistance Informed consent will be obtained from the participants who are willing to take part in the study
- Participants will be clinically and biochemically evaluated for following outcomes

**Primary outcome**: Fasting Insulin Level, HOMA-IR, WHOQOL- BREF, Six minute walk test

**Secondary outcome:** Body composition analysis, Fasting blood sugar, GPAQ, HbA1c.

The participants will be randomized into study group and control group (Block Randomization)

Control Group

Study group

No structured exercise program will be given to the control group participants

Study group participants will be given a set of exercise programs along with the standard care.

Standard hospital care will be advised to the participants

Adherence to exercise will assessed by telephonic call, log book and check list will be given to all the participants

Participants will be asked to continue routine work

After 6 weeks progression of exercise program will be prescribed by the principal investigator

Reassessment of all outcome measures will be done at 3 month

Reassessment of all outcome measures will be done at 3 month

Data will be analyzed

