**CLINICAL SIGNIFICANCE**

- If this study is proved to be effective then structured exercise program can be recommended to reduce insulin resistance in T2DM.

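### The protocol plans no recording or reporting of adverse events or diabetes-medication changes in either arm, yet would recommend the programme on its efficacy results

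*Protocol*

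**What the plan says.** The flowchart under Consort of Phase – I names three activities after randomisation. The first is the adherence check: "Adherence to exercise will assessed by telephonic call, log book and check list will be given to all the participants". The second is a change of programme: "After 6 weeks progression of exercise program will be prescribed by the principal investigator". The third, stated once for each group, is follow-up: "Reassessment of all outcome measures will be done at 3 month".

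The primary outcomes are "Fasting Insulin Level, HOMA-IR, WHOQOL- BREF, Six minute walk test" and the secondary outcomes are "Body composition analysis, Fasting blood sugar, GPAQ, HbA1c". Data analyses provides paired and independent t tests, with descriptive statistics for age, GPAQ and body composition.

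The safety-related text concerns entry. Inclusion criteria restricts the trial to controlled, medicated type 2 diabetes and adds that participants whose "blood glucose level is above 250 mg/dl will be screened for ketone bodies". Exclusion criteria removes people with significant respiratory, coronary, neurological or musculoskeletal disease that would interfere with training. The general guidelines for exercise call for an evaluation before exercise begins.

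The exercise table allows "40-85% HRR [Aerobic Exercise] , 60-80% 1 RM [Resistance Exercise", with aerobic work on three days a week and resistance work on two. Clinical significance states the intended use of the result: "If this study is proved to be effective then structured exercise program can be recommended to reduce insulin resistance in T2DM".

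**The concern.** A recommendation to take up an exercise programme weighs benefit against harm, and this plan collects only the benefit side. Participants take diabetes medication and start a regular programme that changes part-way through, so hypoglycaemia, injury and cardiac symptoms are obvious things to ask about. Nothing in the text has anyone ask.

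The gap cannot be closed later. An analysis plan can say how events are to be tabulated, but it cannot recover events that were never recorded. That is why this belongs in the protocol, and why a statistical analysis plan that is not at hand does not settle it.

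Medication changes raise a second question, about interpretation. Both arms receive standard care, under which diabetes drugs may be altered during the 3 months. Such changes can move fasting insulin, fasting glucose and HbA1c, and HOMA-IR with them, since the Introduction describes it as calculated from fasting glucose and insulin. Without a record, nobody can tell whether they contributed to a difference between arms, or in which direction.

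**Working it through.** The point depends on no figure in the Protocol, so the check is mainly a reading of what is planned at each stage.

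1. **Entry.** Pre-exercise evaluation, ketone screen above the stated glucose level, exclusions. These select participants; they do not observe them during the programme.
2. **Randomisation to 3 months.** Calls, log book and check list, with adherence as the only stated purpose. No call frequency is given, and their contents are not shown.
3. **Six weeks.** Progression is prescribed by the principal investigator. No assessment is tied to it.
4. **Three months.** Four primary and four secondary outcomes are reassessed in both groups. None is an adverse event, hypoglycaemia, injury or cardiac event, and none is a change of medication.
5. **Analysis.** No summary of harms or of medication is listed.

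No section defines, asks about, records or reports adverse events or medication changes.

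A short calculation shows what the planned group size could have told the reader. Inputs: 120 per group and 20% dropout, as stated under Sample size, giving 120 × (1 − 0.20) = 96 completers. The 120 is taken as written. The event rates are assumptions; the Protocol gives none.

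- Upper 95% limit after zero events, 1 − 0.05^(1/n): for n = 120, 1 − 0.05^(1/120) = 2.5%; for n = 96, 1 − 0.05^(1/96) = 3.1%.
- Chance of seeing at least one event at true risk p, 1 − (1 − p)^n:

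| Assumed risk p | n = 120 | n = 96 |
| --- | --- | --- |
| 1% | 70% | 62% |
| 2% | 91% | 86% |
| 5% | 99.8% | 99% |

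The study group is therefore large enough to be informative about harms affecting roughly 2–3% of participants or more, provided someone records them.

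**The case against.** The best counter-argument is that this is silence in a brief protocol rather than an error. Entry is limited to controlled diabetes, interfering disease is excluded, an evaluation precedes exercise, and ethics review is required. The log book and check list may contain more than adherence items, and consent pages, which are not available here, may tell participants to report events. This stands as a caution: adherence is the only *stated* purpose of the contacts, which is not proof that nothing else is asked. It does not supply a plan to collect events alike in both arms or to report them.

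Several stronger readings are tempting and are not supported:

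- *The trial cannot detect harm, and glucose is looked at only at entry.* Fasting blood sugar, HbA1c, the six minute walk and WHOQOL-BREF are measured again at 3 months in both arms, so average worsening could appear. What is missing is individual events.
- *Intensity is raised at 6 weeks.* The text speaks of progression of the programme. The exercise table also leaves room in duration, sets, repetitions and type.
- *Everyone is progressed alike, whatever happened in the first six weeks.* The investigator prescribes the progression and the ranges allow individual prescription. The text is silent on any review beforehand; it does not rule one out.
- *Medication changes differ between arms and spoil the comparison.* Nothing in the Protocol shows that they differ. Changes made after randomisation under standard care do not invalidate the randomised comparison. They affect whether the result is read as the total effect of offering the programme or as an effect of exercise alone.

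**Conclusion.** The point holds as a gap in data collection. The Protocol provides no planned ascertainment, recording or reporting of adverse events or diabetes-medication changes in either arm, while naming a recommendation as the use of a positive result. The consequence is that the report would carry no comparison of individual harms by arm, and no means of judging what medication changes contributed to the four glucose and insulin outcomes.

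No effect estimate or stated figure is shown to be wrong, and the size of any harm or medication difference is unknown. The 2.5% to 3.1% limits only illustrate what is forgone; they assume complete recording in 120 or 96 participants. The conclusion rests on the visible text, including the assumption that the log book and check list contain no event or medication items beyond their stated purpose. The change should be made before recruitment, because data not collected cannot be added afterwards.

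**What to change.** Use the calls, log book and check list already planned to record (a) adverse events, including hypoglycaemia, injuries and cardiac events, and (b) any change of diabetes medication, with drug, dose and date. State the call schedule, and apply the same questions and schedule in both arms, since unequal questioning would itself create a difference in reported events. Add both items to the secondary outcomes and report them by arm in a descriptive table, for example as participants with at least one event and as number of events, with all randomised participants as denominator. If the existing forms already hold such items, the Protocol need only say so and add the reporting.

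For the 6-week progression, the sponsor should note that no assessment is tied to it and address this in the text. No clinical rule is proposed here.

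The cost is slightly longer calls and one more table. Control participants must also be called on the same schedule; the flowchart text does not make clear whether they are called at all at present.
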